### Supervision and fidelity checks

Case conceptualizations and session reports will be checked after each session and feedback will be provided by experts in the field (EMDR therapy: [name]; supportive counseling: [name]; exposure therapy: [name]). Supervisors of exposure therapy are blind to the patient’s condition. Clinicians are instructed to report deviations from the protocol. To further improve treatment integrity, online group supervision sessions are provided for all treatments two to four times a year. Treatment sessions will be recorded on audio (supportive counseling and exposure therapy sessions) or video (EMDR therapy sessions and the behavioral avoidance tasks), unless patients do not give permission for this. An independent rater will assess a selection of the video and audiotapes to assess treatment fidelity.

### Early completion

Early completion is defined as: (1) a score of 0 on weekly assessment scores (General Anxiety Disorder (GAD 7) and Panic Disorder Severity Scale (PDSS-SR) (2) in case of EMDR therapy, a SUD of 0 for all targets part of the case conceptualization (3) and no avoidance on the behavioral avoidance task.

### Instruments

#### Goal 1: investigate whether EMDR therapy + exposure therapy vs supportive counseling + exposure therapy improves treatment efficacy, tolerability, and adherence

The primary and secondary measures to examine goal 1 are presented in Table 1.

**Table 1 Tab1:** Primary and secondary measures to examine goal 1: investigate whether EMDR therapy + exposure therapy vs supportive counseling + exposure therapy improves treatment efficacy, tolerability, and adherence

	**T1**	**Tp1**	**T2**	**Tp2**	**T3**	**FU1**	**FU2**
**Demographics and assessment of eligibility for inclusion**							
Demographics (8)	X	-	-	-	-	-	-
Mini-International Neuropsychiatric Interview Simplified (MINI-S-DSM-5)	X	-	-	-	-	X	-
**Adherence rates**							
Drop out and no-show	-	X	-	X	-	-	-
**Primary outcome: Efficacy panic disorder symptomatology**							
Panic Disorder Severity Scale (PDSS-SR)*(7)	X	X	X	X	X	X	X
Panic Agoraphobia Scale (PAS) (14)	X	-	X	-	X	X	-
Subtle Avoidance Frequency Examination- Agoraphobia (SAFE-A) (40)	X	-	X	-	X	X	X
Fear Questionnaire- Agoraphobia (FQ-A) (5)	X	-	X	-	X	X	X
Bodily Sensation Questionnaire (BSQ) (17)	X	-	X	-	X	X	X

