**Methods:**

A multicenter randomized controlled trial mixed design will be conducted. Participants will be 50 patients, aged ≥ 18, diagnosed with a panic disorder. They will be randomly assigned to one of two conditions: EMDR therapy (i.e., flashforward strategy) or supportive counseling (each consisting of four weekly sessions of 90 min each) prior to exposure therapy (consisting of eight weekly sessions of 90 min each). Assessments will be made pre-treatment (T1), between-treatments (T2), post-treatment (T3), one month post-treatment (FU1) and six months post-treatment (FU2) by an assessor blind to treatment condition. The primary outcome measure is severity of panic-related symptoms. Secondary outcome measures are: tolerability of exposure therapy (initial avoidance, willingness to start exposure therapy, considered drop-out; no-show and drop-out), related symptomatology (generalized anxiety, depression), and functional impairment.

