## Goals of the current study:

The main goal of this multicenter Randomized Controlled Trial is to investigate whether EMDR therapy with exposure therapy, relative to supportive counseling with exposure therapy, improves treatment efficacy, tolerability, and adherence in patients with panic disorder. The primary outcome measures are panic-related symptoms. Secondary outcome measures are: tolerability of exposure therapy (initial avoidance, willingness to start exposure therapy, considered drop-out; no-show and drop-out), related symptomatology (generalized anxiety, depression) and functional impairment. We hypothesize that: (1) EMDR therapy will be more effective in reducing panic-related symptoms, compared to supportive counselling from baseline (T1) to between-treatments (T2). (2) EMDR therapy + exposure therapy will be more effective in reducing panic-related symptoms, compared to supportive counseling + exposure therapy at post-treatment (T3). (3) EMDR therapy will result in higher tolerability of exposure therapy (less initial avoidance, more willingness to start exposure therapy, less considered drop-out; less no-show and actual drop-out) compared to supportive counseling. We further hypothesize that: (4) EMDR therapy will be more effective in reducing related symptomatology (generalized anxiety, depression) and functional impairment, compared to supportive counseling from baseline (T1) to between-treatments (T2). And (5) EMDR therapy + exposure therapy will be more effective in reducing related symptomatology (generalized anxiety, depression) and personal suffering/functional impairment, compared to supportive counseling + exposure therapy at post-treatment (T3).

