### Sample size

For the primary objectives of efficacy, tolerability, and adherence, the sample size was calculated using G*power 3.1 [56] using a 2 (groups) × 2 (time) repeated-measures ANOVA. Given the active control condition, we expect a medium effect size [9]. For a between group effect size of f = 0.25, alpha 0.05, power 0.80, 0.5 correlation among repeated measures and 1.0 non-sphericity correction, a total sample size of 98 participants is needed for two-sided testing. Although no formal method is available to determine a repeated-measures ANOVA sample size using Bayesian statistics, approximations for t-test are available [57]. For a one-sided *t*-test with a power of 0.80 and a Bayes factor of 3 (indicating evidence for the data coming from the alternative than the null hypothesis), 87 participants are needed and for a Bayes factor of 5, 99 participants are needed. Originally, we aimed to recruit 100 participants (see pre-registration: ISRCTN - ISRCTN29668369). However, the COVID-19 pandemic has seriously impacted the number of referrals of patients with panic disorder. To increase the feasibility of the study, we formulated directional hypotheses and decided to use one-sided testing, which reduces our sample size to 50 participants [58]. This change was approved by the ethical committee on February 8 2023. Participants who will not show up to therapy sessions in the first two weeks of treatment will be considered non-compliant and will be described as dropouts. Dropouts will not be excluded from intent to treat analyses, but will be replaced by additional participants to preserve statistical power. The completer sample size will be sufficient to address secondary objectives.

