### Primary outcome variables: efficacy

#### Panic Disorder Severity Scale- self-report form (PDSS-SR):

The PDSS-SR [70–72] is a 7-item questionnaire to assess the severity of panic disorder. Patients rate the frequency, severity and interference of panic attacks in the last week on a 5-point Likert scale (0 = *no interference*, 5 = *extreme interference*).

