### Data analysis

Data of all randomized participants will be analyzed on intent-to-treat basis as well as the completer sample. The primary outcomes (panic disorder symptomology) as well as secondary outcomes (tolerability and adherence) will be analyzed using a mixed regression model, using baseline scores as a covariate. This enables us to identify any fixed or random effects resulting from the treatments and changes over time. To analyze count date (e.g., drop-out, no show), Poisson or negative binomial regression will be used. Data analysis strategies for the secondary goals (goals 2–4) will be pre-registered in prior to analysis in Open Science Framework [52].

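### Five instruments are labelled primary and two unranked hypotheses apply to them, with no lead instrument or time point named, so the error rate of the primary claim is not held at 5%

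*Protocol article*

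**What the plan says.** The abstract gives a construct in the singular: "The primary outcome measure is severity of panic-related symptoms". The section on the goals of the study gives the same construct in the plural: "The primary outcome measures are panic-related symptoms". Neither names an instrument.

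The instruments appear in Table 1 under "Primary outcome: Efficacy panic disorder symptomatology": PDSS-SR, PAS, SAFE-A, FQ-A and BSQ. The instrument descriptions repeat the same five under "Primary outcome variables: efficacy". PDSS-SR carries an asterisk in Table 1, but the table note does not explain it.

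The goals section attaches two numbered hypotheses to panic-related symptoms. Hypothesis 1 compares EMDR with supportive counseling from T1 to T2. Hypothesis 2 compares the two full sequences, each including exposure therapy, at T3. Neither is ranked above the other.

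The Sample size section powers a single 2 × 2 repeated-measures ANOVA effect with "alpha 0.05, power 0.80, 0.5 correlation among repeated measures" and f = 0.25. It then moves to directional hypotheses and one-sided testing, with 50 participants. Under Data analysis: "The primary outcomes (panic disorder symptomology) as well as secondary outcomes (tolerability and adherence) will be analyzed using a mixed regression model", with baseline as covariate. The article states no rule for what counts as success on the primary outcome.

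**The concern.** Which outcome is primary is something a protocol itself settles, and this one settles it with five co-equal instruments at two co-equal time points. The five are not five readings of one scale. They cover self-rated severity, interview-rated severity, subtle avoidance, avoidance of places and fear of bodily sensations, so they can disagree. Read as written, up to ten group comparisons bear on the primary claim, and any of them could later be presented as the primary result.

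Because testing is one-sided in favour of EMDR, every false positive points the same way. The sample size makes no provision for several primary comparisons. What is at stake is the meaning of a positive trial: a nominal 5% error rate holds for one pre-named comparison, not for a free choice among ten.

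**Working it through.** **Inputs from the article.** Five instruments (Table 1); two time points, T2 and T3 (hypotheses 1 and 2); alpha 0.05, power 0.80, f = 0.25 and a correlation of 0.5 among repeated measures (Sample size); one-sided testing (Sample size).

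**Inputs assumed.** Correlation between instruments 0.3–0.7, with 0.2, 0.8, 0.9 and independence as checks; between-time correlation 0.3–0.7 around the article's 0.5; alpha kept at 0.05 after the move to one-sided tests; any one significant result counts as success.

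**Step 1: the plan's own figure covers one test.** For the between-group effect, λ = f²·N·m / (1 + (m − 1)ρ). With N = 98, m = 2 and ρ = 0.5, λ = 0.0625 × 98 × 2 / 1.5 = 8.17. The noncentral F test with 1 and 96 degrees of freedom then has power 0.808. The stated 98 for two-sided testing is reproduced, and it belongs to one F test of one outcome.

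**Step 2: independence, as the upper reference.** The chance of at least one false positive in k tests is 1 − 0.95^k.

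- Five tests: 1 − 0.95⁵ = 22.6%.
- Ten tests: 1 − 0.95¹⁰ = 40.1%.

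**Step 3: correlated tests.** Ten standard normal statistics (5 instruments × 2 times) were simulated under no effect anywhere, 300,000 draws per setting or more. The correlation of two statistics is the instrument correlation times the time correlation. The result is the share of draws with at least one statistic above 1.645.

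| Instrument correlation | Five tests, one time point | Ten tests, time corr. 0.3 | Ten tests, 0.5 | Ten tests, 0.7 |
|---|---|---|---|---|
| 0.2 | 20.5% | 35.0% | 33.3% | 30.7% |
| 0.3 | 19.2% | 33.1% | 31.5% | 29.1% |
| 0.5 | 16.6% | 28.7% | 27.1% | 25.0% |
| 0.7 | 13.6% | 23.6% | 22.2% | 20.4% |
| 0.8 | 11.7% | 20.6% | 19.4% | 17.9% |
| 0.9 | 9.5% | 17.0% | 16.2% | 14.6% |

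Over correlations of 0.3–0.7, the range is 13.6–19.2% per hypothesis and 20.4–33.1% over both.

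**Step 4: what naming a lead does.**

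- One instrument tested at both T2 and T3, each at one-sided 5% with no ordering: 8.0–9.3% (time correlation 0.7–0.3).
- One instrument at one time point: 5%. Testing the other time point only after success at the first keeps this at 5%, because with no effect anywhere a false claim first requires a false rejection at step one.
- For comparison, all ten tests at 0.05/10 = 0.005 each: 3.2–4.3% (time correlation 0.5, instrument correlation 0.7–0.3).

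**The case against.** Several counter-arguments have force.

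- *The tests are inferred.* Data analysis describes a mixed model, not ten tests, and no text says that one significant instrument suffices. A composite, or a rule requiring several instruments to agree, would give a different error rate. This stands, so the percentages must be conditional on an any-one-counts rule. Nothing in the article excludes that rule either.
- *Pooling T2 and T3 is a choice.* The hypotheses are numbered separately and concern different contrasts. This stands, so the per-hypothesis figure belongs beside the pooled one. It is still well above 5%.
- *Alpha is not restated as one-sided.* The value 0.05 appears in the two-sided calculation, and Bayes-factor sample sizes are also quoted. One-sided 0.05 is the natural reading, but it is a reading.
- *A testing order or adjustment may sit in the analysis plan.* That is possible, and its absence here is not the point. The point is that the article itself designates five primaries. The asterisk on PDSS-SR might mark a lead measure, but it cannot be relied on without an explanation.

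A reader might also infer that the abstract contradicts Table 1 by naming one measure. It does not: it names a construct without an instrument, which is underspecification. Nor do the documents show that this is the main route to a spurious positive result, since no other source of error has been weighed against it.

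**Conclusion.** The point holds: the primary claim rests on five co-equal instruments and two unranked hypotheses, and following the article as written does not control its error rate at 5%. Across the instrument correlations examined, the result is roughly two to four times nominal within one hypothesis and roughly three to seven times nominal over both under the any-one-counts rule.

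It would go too far to quote 20–33% as the trial's error rate. That range depends on instrument correlations the article does not give, on a success rule it does not state, on pooling two separately numbered hypotheses, and on alpha staying at 0.05 one-sided. Even at an instrument correlation of 0.9, however, the rate exceeds 5%: about 9.5% for one hypothesis and 15–17% for both.

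**What to change.** Before any analysis, state in the protocol and analysis plan:

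1. One primary instrument at one primary time point. Baseline-adjusted PDSS-SR at T3 is one option; PAS at T3 is another if an interview by a blinded assessor is preferred to self-report. The article does not settle this choice. PDSS-SR is collected at every assessment and during both treatment phases, while PAS is the only interview among the five and is not collected at FU2.
2. The same instrument at the other time point, tested next in a fixed sequence at the same alpha and only if the first test succeeds. State the alpha and sidedness explicitly.
3. The other four instruments as secondary, reported with confidence intervals.

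The cost is in status and not in data: four instruments lose primary rank, and the second hypothesis is tested formally only if the first succeeds. With T3 first, the direct EMDR-versus-counseling contrast at T2 would depend on a difference persisting after both arms have received exposure therapy, so the order should be chosen deliberately. The named test keeps its full alpha and so loses no power. Whether 50 participants give that test enough power is a separate question. The article reports that recruitment is ongoing and that no datasets have been generated or analyzed, so the change can still be made in advance.

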**Secondary outcomes: Tolerability of exposure therapy**							
Exposure willingness (1)	-	X	-	X	-	X	X
Intention to stop treatment (1)	-	-	X	-	X	-	-
Behavioral avoidance task	-	-	-	X	-	-	-
**Secondary outcomes****: ****Related symptomatology and functional impairment**							
General Anxiety Disorder 7 (GAD 7) (7)	X	X	X	X	X	X	X
Patient Health Questionnaire (PHQ-9) (9)	X	X	X	X	X	X	X
Work and Social Adjustment Scale (WSAS) (5)	X	-	X	-	X	X	X
**Secondary outcomes****: ****Treatment satisfaction**							
Client Satisfaction Questionnaire (CSQ-8) (8) and Net Promotor Score (NPS) (1)	-	-	X	-	X	-	-

Note: *(nr.)* number of items, *T1* Baseline, *Tp1* Treatment phase 1 *(EMDR therapy or supportive counseling) T2* Between-treatments, *Tp2* Treatment phase 2 (exposure therapy), *T3* Post-treatments, *FU1* follow-up 1, *FU2* follow-up 2

### Demographics and study eligibility

#### Demographics:

Eight demographic variables will be assessed: age, sex, cultural background, educational level, native language, marital status, familiarity with the treatments and age of panic disorder onset.

#### Mini-International Neuropsychiatric Interview-Simplified for DSM-5 (MINI-S-DSM-5):

To assess panic disorder and other diagnoses, the Dutch translation [67] of the MINI-S- interview [68, 69] version 1.1 (adapted to DSM-5) is administered by an independent psychologist.

### Primary outcome variables: efficacy

#### Panic Disorder Severity Scale- self-report form (PDSS-SR):

The PDSS-SR [70–72] is a 7-item questionnaire to assess the severity of panic disorder. Patients rate the frequency, severity and interference of panic attacks in the last week on a 5-point Likert scale (0 = *no interference*, 5 = *extreme interference*).

#### Panic *Agoraphobia Scale (PAS)*:

The PAS [73] is a 14-item interview to assess panic disorder severity. The severity of panic disorder is rated using a 5-point Likert scale (0 = *not at all*, 4 = *severe*) for each item. As a minor addition the frequency of panic attacks as well as the number of avoided places is registered.

#### Subtle Avoidance Frequency Examination – agoraphobia (SAFE-A):

The SAFE-A is a 40-item questionnaire to assess the frequency of subtle avoidance behavior in agoraphobia [74, 75], using a 5-point Likert scale (0 = *never*, 5 = *always*) and when safety behavior is performed on a 3-point Likert scale (1 = *before the situation*, 2 = *during the situation*, 3 = *during a panic attack*).

#### Fear Questionnaire-*Agoraphobia (FQ-A)*:

The FQ-5 [76, 77] is a 5-item questionnaire to assess avoidance behavior for various places (e.g. busy shop, public transport), using a 9-point Likert scale (0 = *I never avoid this*, 8 = *I always avoid this*).

#### Bodily Sensation Questionnaire (BSQ):

The BSQ [78] is a 17-item questionnaire to assess fear of bodily sensations in panic disorder, using a 5-point Likert scale (1 = *not afraid*, 5 = *extremely afraid*).

### Secondary outcome variables: Tolerability of exposure therapy

#### Willingness to start exposure therapy:

Willingness to start exposure therapy will be assessed with one item developed for this study using a Visual Analogue Scale (VAS) (0 = *not willing to do all exposure exercises,* 100 = *willing to do all exposure exercises*).

#### Intention to stop treatment:

Intention to stop treatment will, retrospectively after treatment, be assessed with one item developed for this study, using a VAS (0 = *not at all,* 100 = *very much*).

#### Behavioral avoidance task:

Behavioral avoidance will be assessed with a standardized task during the first and last exposure therapy session, in which the patient is exposed to self-induced bodily sensations (e.g., self-induced dizziness, accelerated heart rate and hyperventilation or physical exercises) [79]. Clinicians rate the level of avoidance on a standardized scale (developed for this study) based on the number of tasks completed and task difficulty. Afterwards, videotapes will be rated with the same scale by blind assessors.

### Secondary outcome variables: Related symptomatology and functional impairment

#### General Anxiety Disorder 7 (GAD-7):

The GAD-7 [80, 81] is a 7-item questionnaire to measure the frequency of anxiety symptoms on a 4-point Likert scale (0 = *not at all*, 3 = *almost every day*) for the past week.

#### Patient Health Questionnaire (PHQ-9):

The PHQ-9 [81–83] is a 9-item questionnaire measuring the frequency of depression symptoms on a 4-point Likert scale (0 = *not at all*, 3 = *almost every day*) for the past week.

#### Work and Social Adjustment Scale (WSAS):

The WSAS [84, 85] is a 5-item self-report questionnaire to assess disability in daily life (e.g., work, home management, social activities) on a 9-point Likert scale (0 = *no disability*, 8 = *severe disability*).

### Secondary outcome variables: Treatment satisfaction

#### Client Satisfaction Questionnaire (CSQ-8):

The CSQ-8 [86–88] is an 8-item self-report questionnaire to assess treatment satisfaction on a 4-point Likert scale (1 = *totally disagree*, 4 = *totally agree*).

#### Net Promoter Score (NPS):

Patients are asked to give an overall grade for the treatment [89], on an 11-point Likert scale (0 = *very bad treatment*; 10 = *very good treatment*).

#### Instruments goal 2: unravel theory-driven variables (e.g., traits and clinical profiles) and non-specific patient and therapist factors predicting treatment outcome and optimal treatment allocation

Table 2 presents additional measures to examine secondary goals.

**Table 2 Tab2:** Additional measures to test goal 2: unravel theory-driven variables (e.g., traits and clinical profiles) and non-specific patient and therapist factors predicting treatment outcome and optimal treatment allocation

	**T1**	**Tp1**	**T2**	**Tp2**	**T3**	**FU1**	**FU2**
***Questionnaires for all patients***							
Survey of Autobiographical Memory (SAM) (14)	X	-	-	-	-	-	-
Impact of Event Scale past (15)/future (15)	X	-	X	-	X	X	X
List of Threatening Experiences (LTE) (12)	X	-	-	-	-	-	-
Dutch credibility and expectancy scale (CEQ) (8)		X		X	-	-	-
Working Alliance Inventory-12 (WAI-12) (12)	-		X		X	-	-
Intolerance of Uncertainty Scale (IUS) (12)	X	-	-	-	-	-	-
Anxiety Sensitivity Index (ASI) (18)	X	-	-	-	-	-	-
Penn State Worry Questionnaire (PSWQ) (16)	X	-	-	-	-	-	-
***Computer task***							
De novo fear conditioning task	X	-	-	-	X	-	-
***Questionnaires for all therapists***							
Demographics (10)	X	-	-	-	-	-	-
Attitudes Toward Psychotherapy Treatment Manuals (ATPTM) (19)	X	-	-	-	-	-	-
Evidence-Based Practice Attitude Scale (EBPAS) (15)	X	-	-	-	-	-	-
Credibility Scale (CS) (5)	X	-	-	-	-	-	-
Predicting treatment outcome survey (9)	-	X	-		-	-	-
Working Alliance Inventory-12 (WAI-12) (12)	-	X	-	X	-	-	-
Optimal exposure (2)	-	-	-	-	X	-	-
***Assessment therapists***							
Treatment integrity session reports	-	X	-	X	-	-	-

*Note: (nr.)* number of items, *T1* Baseline*, Tp1* Treatment phase 1 (EMDR therapy or supportive counseling)*, T2* Between-treatments*, Tp2* Treatment phase 2 (exposure therapy)*, T3* Post-treatments*, FU1* follow-up 1*, FU2* follow-up 2

### Patient predictors, mediators and moderators

#### Survey of Autobiographical Memory (SAM)>:

The SAM [90] is a self-report inventory designed to assess naturalistic episodic autobiographical, semantic and spatial memory, as well as prospection or future thinking using a 5-point Likert scale (1 = *strongly disagree*, 5 = *strongly agree*). We include the episodic and future thinking subscales only (14 items).

#### Impact of past event scale (IES):

The IES [91, 92] is a 15-item questionnaire to assess the frequency and avoidance of intrusive mental imagery of past events in the last week, using a 5 point Likert scale (1 = *not at all*, 5 = *extremely*).

